#### Exclusion criteria

Potential participants are screened for evidence of serious low back pathology and for contraindications to exercise therapy by a physical therapist. They are excluded prior to randomization if they had neurological signs (leg weakness), specific spinal pathology (e.g. malignancy, or inflammatory joint or bone disease) or if they had undergone back surgery. The aim of the measurement of DEPS, TSK and MCAQ is to rule out those patients with LBP of non-mechanical origin, e.g. depression, fear-avoidance and a poor ability to learn exercises. The aim of physical examination of SLR and sacroiliac-joint provocation tests is to rule out those patients with mechanical movement impairment [60].

### Randomization

Each participant is randomized to a general exercise group or a SMCE group. Randomization will be done with the Randomizer 17.0 program. The randomization schedule is known only to one investigator who is not involved in recruiting participants, and it is concealed from patients and the other investigators using consecutively numbered, sealed, opaque envelopes. The physiotherapists treating the participants are not involved in the randomization process.

Baseline assessment of each group will be taken to ensure they are not different.

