### Outcome measures

Baseline measures are taken of the one primary outcome (RMDQ), and four secondary outcomes (PSFS and Oswestry Disability Index, Movement control tests by Luomajoki, general health questions) prior to randomization.

Main outcome measure:

Roland-Morris Disability Questionnaire (RMDQ)

Secondary outcome measures:

Patient-Specific Functional Scale (PSFS) [61]

Oswestry Disability Index [62]

Movement control tests described by Luomajoki et al. [47]

The amount of absence from work with a questionnaire#

The need for other treatment modalities with a questionnaire#

The need for pain medication with a questionnaire#

Patient satisfactory with global assessment with a questionnaire#

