# A questionnaire with three claims (less than usual, equal, more than usual)

### Statistical analysis

A sample size of 70 participants, determined a priori, provides 80% power by α 0.05 to detect an effect of change in disability based on three point difference with RMDQ, which we regard as minimal important difference for this outcome [63].

The comparability of the groups on prognostic and outcome variables at baseline will be analyzed using the two-sample t-tests for parametric and Wilcoxon test for non-parametric distribution as well as Chi-Square test for nominal data. Differences between the groups over time are measured with Mann Whitney *U *test. A regression analysis for predictive factors will be conducted on covariates at baseline. Statistical significance is set on α < 0.05. Statistical analyses will be done with SPSS for Windows release 17.0.

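### Baseline significance tests cannot show that the two groups are alike, and the between-group comparison that follows makes no use of baseline RMDQ

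*Protocol article*

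**What the plan says.** The Randomization section describes a schedule concealed in numbered, sealed, opaque envelopes and then states the purpose of the baseline comparison: "Baseline assessment of each group will be taken to ensure they are not different". It describes no stratification or balancing on baseline RMDQ.

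The Statistical analysis section gives the means: "The comparability of the groups on prognostic and outcome variables at baseline will be analyzed using the two-sample t-tests", with a Wilcoxon test for non-parametric distributions and a chi-square test for nominal data. Differences between the groups over time are then assessed with a Mann-Whitney U test. Baseline covariates appear only in a separate regression that looks for predictive factors; it is not named as the treatment comparison.

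On size, the same section sets N = 70 for a power of 80% at α = 0.05, the target being "an effect of change in disability based on three point difference with RMDQ". No SD, correlation, allocation ratio or sidedness is given. The Outcome measures section confirms that RMDQ is recorded before randomisation.

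**The concern.** Two things go wrong together.

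First, the tests cannot do the job assigned to them. When allocation is random and concealed, any baseline difference arises by chance, so the hypothesis under test is already known to be true. A non-significant result in a trial of this size does not show that the groups are alike.

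Second, whatever imbalance exists remains in the result, because the named comparison ignores baseline RMDQ. Given an imbalance on a prognostic variable, the unadjusted contrast is off by a predictable amount. Even without imbalance, it discards information that would narrow the confidence interval. At stake are how far the observed RMDQ difference can be read against the 3-point target, and power that the trial could have at no extra cost.

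**Working it through.** **Inputs**
- From Statistical analysis: N = 70, power 80%, α = 0.05 ("Statistical significance is set on α < 0.05"), target 3 RMDQ points.
- Assumed: 35 per arm, two-sided testing, baseline SD 3 to 5, baseline-outcome correlation r = 0.3 to 0.7.

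**Step 1: the plan's own sample size.** Without an SD, N = 70 cannot be reproduced, only solved backwards. With √(2/35) = 0.2390:

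SD = 3 / [(1.960 + 0.842) × 0.2390] = 4.48 by the normal approximation, or 4.42 by the t-test.

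This is the SD of whatever score the sample size was based on. Using it for baseline RMDQ is an assumption.

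**Step 2: what passes the check.** The largest non-significant difference is t(0.975, 68) × √(2/35) = 1.995 × 0.2390 = 0.477 SD. This needs no assumed SD. In points:
- SD 3: 1.43
- SD 4.48: 2.14, which is 71% of 3 points
- SD 5: 2.39

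At SD 4.48, the baseline t-test would flag a true difference of 2 points with a probability of only about 45%, and one of 1 point with about 15%.

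**Step 3: shift in the unadjusted contrast at that boundary.** For follow-up scores with equal SDs at baseline and follow-up, the expected shift in the mean difference is r × imbalance.

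| Baseline SD | r = 0.3 | r = 0.5 | r = 0.7 |
|---|---|---|---|
| 3 | 0.43 (14%) | 0.72 (24%) | 1.00 (33%) |
| 4.48 | 0.64 (21%) | 1.07 (36%) | 1.50 (50%) |
| 5 | 0.72 (24%) | 1.19 (40%) | 1.67 (56%) |

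Entries are points, with the percentage of the 3-point target. For change scores the shift is (1 − r) × imbalance in the opposite direction: the same size at r = 0.5, with the ends of each row exchanged. The Mann-Whitney test does not estimate a mean difference, so these figures indicate the displacement it would face.

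**Step 4: how often.** At SD 4.48 the standard error of the baseline difference is 4.48 × 0.2390 = 1.071. A shift of at least 1 point in follow-up scores needs an imbalance of at least 1/r. The chance of reaching that and still passing is 2 × [1 − Φ((1/r)/1.071)] − 0.05, set to 0 if negative:
- r = 0.3: 0
- r = 0.5: about 1%
- r = 0.6: about 7%
- r = 0.7: about 13%

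A one-standard-error imbalance at r = 0.5 gives 0.5 × 1.071 = 0.54 points, or 18% of the target.

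**Step 5: what adjustment gains.** If 4.48 is the follow-up SD, the residual SD after adjustment is 4.48 × √(1 − r²), and power is Φ(3 / [residual SD × 0.2390] − 1.96):
- r = 0.3: residual SD 4.27, power 0.84
- r = 0.5: residual SD 3.88, power 0.90
- r = 0.7: residual SD 3.20, power 0.98

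The planned figure is 0.80. If 4.48 is instead the SD of change, with equal SDs at both times, the residual SD is 4.48 × √((1 + r)/2) = 3.61, 3.88 and 4.13. Power is then 0.94, 0.90 and 0.86, so adjustment gains on either reading.

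**The case against.** The strongest objection is that the baseline tests alter no estimate. No action is attached to their result, and the Mann-Whitney comparison goes ahead either way. Deleting them would leave every imbalance where it was. This stands: the shifts above belong to the missing adjustment, not to the tests.

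A reader might infer that the primary result stands to be off by about a third of the target effect. The documents do not support that as an expectation. It takes an imbalance almost at the significance boundary, r near 0.5, and a baseline SD near a value that the article never states. The sample size is tied to a change in disability, so the implied SD may be that of change, and the entry floor of 5 RMDQ points may narrow the baseline spread. At r = 0.3 and SD 4.48 the maximum is 21%.

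A reader might also infer a high rate of false alarms. Ten independent tests would give 1 − 0.95^10 = 40%, but the article gives no count, and RMDQ, Oswestry and PSFS all concern function or disability, so independence is implausible. Nor does any stated rule lead from a significant baseline test to a data-driven adjustment.

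Finally, the regression on baseline covariates might be detailed elsewhere as an adjusted comparison. The article describes it as a search for predictors and names a different test for the group difference, so it does not answer the point as written.

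**Conclusion.** The concern holds in a limited form. The stated purpose cannot be met by the stated tests: at 35 per arm, differences of up to 0.477 SD pass. That rests only on equal allocation and two-sided testing.

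The practical cost comes from leaving the comparison unadjusted. It is bias conditional on the imbalance that happens to arise, together with lost precision. Chance imbalance under concealed randomisation does not inflate the unconditional type I error, so the planned test is not invalid.

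The boundary shift of 14% to 56% of the target is a rare worst case under assumed SDs and correlations; about 18% is a more ordinary figure at r = 0.5. The point is worth acting on because the remedy uses a measurement already planned and improves precision whatever imbalance occurs.

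**What to change.** - In Randomization, remove the sentence about ensuring that the groups are not different. In Statistical analysis, remove the baseline significance tests. Report baseline values by arm descriptively: mean and SD, median and interquartile range, or counts.
- Prespecify that the primary between-group RMDQ comparison is adjusted for baseline RMDQ, for example by ANCOVA, whatever imbalance is seen. Keep the Mann-Whitney U test as a sensitivity analysis.
- State that the regression for predictive factors is separate from this comparison.

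The cost is more than a wording change, because the primary analysis has to be restated, and this should be done before outcome data are examined by arm. No new data are needed: baseline RMDQ is already collected, and regression in the named software is already planned.

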### Interventions

Participants attend for up to five treatment sessions over an eight week period. The treatment is carried out by two different physiotherapists. The treatments are implemented as follows.

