This study has several limitations. The treating physiotherapist or subjects cannot be blinded, however because there is no accepted standard therapy, it is not truly known which therapy is better. The amount of the home exercises is totally dependent the motivation of the subject to perform the given exercise program which could influence the outcome of this study. Core stability represents a spectrum of exercises [64]. The comparison group includes a group of core stability exercises, core stiffness exercises, that involves an element of control of the spine. This means that both groups have an intervention that is cognitively attempting to control the position of the spine, although they also have fundamental differences in their application and potential benefits. This study includes subjects with recurrent, sub-acute LBP. Some of these individuals may spontaneously recover [4]. With a small sample size, the results would have to be interpreted with caution. There are several aspects of the study which influence the external validity. The application of the interventions within the study relies on the skills of the treating physiotherapist. Physiotherapists could learn to teach general exercise program, but the assessment and rehabilitation of MD is not taught in all undergraduate courses and post graduate training is required. This study will use five treatment sessions, however it may take longer for some patients to learn the SMCE well enough to change the movement patterns and decrease disability. In practice, greater than five sessions is likely possible, however if the SMCE are not effective in reducing disability, it is not known what would happen with a longer rehabilitation time frame with more sessions. In clinical practice, time and costs often limit the time that a physiotherapist can spend with a patient. It may not be appropriate to physiotherapists to spend forty-five minutes with patients as was done in this study. This could influence the application of learning the SMCE.

The main study question is which of the two exercise programs is more effective in reducing the disability associated with LBP.

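### Two physiotherapists deliver all treatment and the planned test cannot account for therapist; the loss is small if both treat both arms, but therapist and program cannot be separated if each treats one

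*Protocol article*

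**What the plan says.** Under Interventions, ahead of the separate descriptions of the two programs, the article states "The treatment is carried out by two different physiotherapists". Neither that section nor the program descriptions link a physiotherapist to an arm.

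Under Randomization, the unit is the individual: "Each participant is randomized to a general exercise group or a SMCE group". The schedule is computer-generated ("Randomization will be done with the Randomizer 17.0 program") and concealed in numbered envelopes. The therapists are mentioned only to say that "The physiotherapists treating the participants are not involved in the randomization process".

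Under Statistical analysis, the comparison is fixed: "Differences between the groups over time are measured with Mann Whitney" U test. The only model mentioned is exploratory: "A regression analysis for predictive factors will be conducted on covariates at baseline". Physiotherapist is not named there.

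The Discussion says that "The application of the interventions within the study relies on the skills of the treating physiotherapist" and that "the assessment and rehabilitation of MD is not taught in all undergraduate courses and post graduate training is required", whereas the general program is described as something physiotherapists could learn to teach. Both remarks are offered as matters of external validity.

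**The concern.** The trial has two arms and two people delivering treatment, and it asks which exercise program reduces disability more. Therapist skill can affect outcome apart from the type of exercise. Each 45-minute session in either arm includes 10 to 15 minutes of manual therapy, part of the movement control content is left to the physiotherapist's decision, and the physiotherapists are not blinded. The Discussion also describes unequal training needs for the two programs, which makes it conceivable that each program was given by a different person.

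The article treats dependence on skill as a question of generalisability. With only two therapists it is first a question of internal validity, and its weight depends on who treats whom. In a crossed arrangement therapist is an ordinary prognostic factor that the analysis leaves out. In a nested arrangement (one therapist per arm) the difference between two individuals enters the treatment estimate in full, and recruiting more patients under the same two people does not reduce it. Keeping therapists out of randomization protects concealment, but it does not balance therapist across arms.

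**Working it through.** **Inputs from the article.** Two physiotherapists, two arms, N = 70, 80% power, alpha 0.05, target difference 3 RMDQ points.

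**Assumptions, none stated in the article.** Equal allocation (35 per arm), a two-sided test, the normal approximation, and a therapist ICC of 0.01, 0.02 or 0.05.

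**The plan's own figure.** No SD is given, so N = 70 cannot be reproduced directly. The SD that it implies is

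SD = 3 / [(1.960 + 0.842) × √(2/35)] = 3 / (2.802 × 0.2390) = 4.48 points.

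This back-solved SD is itself an assumption and serves only to express results in RMDQ points. The standard error of the arm difference is 4.48 × 0.2390 = 1.07 points.

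**Case A: one therapist per arm.** In units of the total variance, the arm difference has a within-therapist variance W = (1 − ICC) × 2/35, which is all that the test can see, and a between-therapist variance B = 2 × ICC, which it cannot see. The type I error of the nominal 5% test is 2 × [1 − Φ(1.96 × √(W/(W + B)))]. The SD of the difference between two therapists is 4.48 × √(2 × ICC). The type I error does not depend on the value of 4.48.

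| Assumed ICC | W | B | 1.96 × √(W/(W+B)) | Type I error | SD of therapist difference (points) |
|---|---|---|---|---|---|
| 0.01 | 0.0566 | 0.02 | 1.685 | 0.092 | 0.63 |
| 0.02 | 0.0560 | 0.04 | 1.497 | 0.134 | 0.90 |
| 0.05 | 0.0543 | 0.10 | 1.163 | 0.245 | 1.42 |

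The same point without an ICC: a fixed therapist difference of 1 or 2 points (assumed), with no true difference between programs, would give a significant result in about 15% or 46% of such trials.

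**Case B: both therapists treat both arms, half the patients each (assumed).** Participants are randomized individually, so the Mann-Whitney test keeps its error rate. Under simple randomization, the between-arm difference in the share treated by one therapist has SD √(0.25 × 2/35) = 0.12. Multiplying by the SD of the therapist difference gives the typical chance shift in the estimate: 0.12 × 0.63 = 0.08 points at ICC 0.01, and 0.12 × 1.42 = 0.17 points at ICC 0.05.

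If adjustment removed the full therapist share of the variance, power would rise from 0.80 to 0.804 at ICC 0.01 and to 0.820 at ICC 0.05.

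**The case against.** The strongest reply is that the concern argues from silence. The sentence on staffing covers both programs and ties nobody to an arm. This is a condensed journal article, and the full protocol may state who treats whom and whether allocation was stratified. A reader might infer from two arms, two therapists and the remark on postgraduate training that delivery followed arm and that the trial is confounded. The documents do not support that. The training remark concerns undergraduate courses in general, and it does not say that the two trial therapists differ in skill or training. What the Discussion says relies on skill is application of the interventions; it does not say that outcomes differ by therapist. All of this stands, so confounding is a possibility and not a finding.

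It is also fair that the inflated error rates need both an assumed arrangement and an assumed ICC, and that on the crossed reading only a modest gain in precision is at issue.

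The reply does not dispose of the point. The article does fix the number of therapists and a rank test that cannot adjust for them, while saying that delivery rests on their skill. Whatever the full protocol says about assignment, the stated comparison ignores therapist.

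**Conclusion.** The point holds in conditional form. What the article establishes is that two therapists deliver all treatment, that delivery is acknowledged to rely on their skill, and that the named test cannot account for them. What it leaves open is whether they are crossed with the arms.

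- **If crossed,** the planned test is valid and the loss is small: a typical chance shift of about 0.08 to 0.17 points against a target of 3, and at most about two percentage points of power, for ICCs of 0.01 to 0.05.
- **If delivery follows arm,** program and therapist are the same variable. No analysis can separate them, and the main study question could not be answered as posed. The 9% to 24% type I error is a worst-case illustration of this arrangement only. It rests on one therapist per arm, 35 patients each and an assumed ICC, and it is not an estimate of the error rate of this trial.

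On either reading the change needed is cheap, which is why the point is worth acting on.

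**What to change.** 1. State who treats whom. Have both physiotherapists treat participants in both arms, and assign the participant to a physiotherapist before the envelope is opened, so that the choice of therapist cannot depend on the allocation.
2. Replace or supplement the Mann-Whitney test with a linear model of follow-up RMDQ on arm, baseline RMDQ and physiotherapist. Enter physiotherapist as a two-level fixed factor, because two therapists are too few to estimate a random-effect variance usefully.
3. If delivery has in fact been one therapist per arm, say so, report the contrast as program plus therapist, and do not attribute it to exercise type. Adding a therapist term cannot help in that case.

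New envelope sequences stratified by physiotherapist are optional and not needed for this fix. Recruitment was planned from October 2010 to about November 2012, so sequences introduced part-way would cover only the remaining participants, and they would balance the arms within therapist only if blocked.

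**Cost.** Some protocol wording and one degree of freedom for the physiotherapist term. Both physiotherapists must be competent in both programs, and there is some risk of carry-over between programs when one person delivers both. No extra staff are required.

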### Initial assessment

A physical therapist carries out an initial assessment of each participant allocated to the exercise group to determine how physically active the participant is, how troublesome the back problem is, and the ability of the participant to perform the exercises. These are measured by the treating physiotherapist by asking the participant.

#### General exercise

Participants are taught the exercises and advised of the intensity at which they should exercise. The exercises are performed under supervision of a physical therapist. The intensity of the exercises is progressed over the 5 treatments with participants being encouraged to improve their own performance. Each session lasts 45 min and includes a short session (10-15 minutes) of manual therapy. Home exercises are taught and the ability to perform them is controlled in each treatment session. The participant performs the previously taught exercises and the physiotherapist corrects the performance if necessary. Home exercises are instructed to be performed three times a week.

The main aims of the program are to improve physical function and confidence in using the spine. The program targeting at abdominal and paraspinal muscles without the involvement of the deep muscles activation was described by McGill [22] and was investigated by Koumantakis et al. (2005) [19].

#### Specific movement control exercise

Participants are taught the SMCE and advise of the intensity at which they should exercise. The exercises are performed under supervision of a physical therapist. The participant performs the previously taught exercises and the physiotherapist corrects the performance if necessary. In addition the movement control is taught with sitting position exercises, four point kneeling and standing exercises according to the decision of the physical therapist to be performed once or twice daily. The intensity of the exercises is progressed over the 5 treatments with participants being encouraged to improve their own performance. Each session lasts 45 min and includes a short session (10-15 minutes) of manual therapy. Home exercises are taught and the ability to perform them is controlled in each treatment session. Home exercises are taught to be performed three times a week and the sitting, four point kneeling and standing exercises are taught to be performed once or twice daily.

The main aims of the program are to improve the individual direction specific movement control of the lumbar spine, physical function and confidence in using the spine.

The main difference between the two exercise groups is individual and also cognitive learning, because in SMCE group the participants also learn how to move and use their back Figure 1.

